### Data Safety Monitoring Board (DSMB)

Serious adverse events (SAE) as described above and unexpected SAE will be collected for the first 72 hours from initiation of auto-BPAP. All SAEs will be reported by fax or Email within 24 hours from occurrence to the DSMB that is composed of two clinicians and a biostatistician at the University of Technology Dresden who is not involved in the execution of this study. In the event of an SAE, subjects in the auto-BPAP arm will immediately have the procedure terminated, and will receive stabilizing procedures. All SAEs must be reported within 24 hours, and will require submission of incident findings and associated events by the local principal investigator to the DSMB for adjudication. From our pilot study [36], we expect SAEs to occur in less than one in ten enrolled patients. If there is one SAE in the first 10 patients, the study will continue. If there are two SAEs in the first 10 patients then the study will stopped and DSMB will make recommendations if certain criteria/exposures need to be modified. The study will be halted if treatment with auto-BPAP results in more than two SAEs per 10 patients. Thereafter, DSMB will receive monthly enrollment/safety/outcomes reports. Additionally, DSMB will be convened any time that safety or data concerns arise. DSMB will also have access to unblinded data, to make decisions if higher than expected rates of SAEs are being outweighed by potential benefits; no further criteria for stopping the trial will be set as limited data are available to guide such algorithms at this point.

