### Randomization

All randomization procedures are prepared and monitored by the Dresden Coordination Center for Clinical Studies, independent of patient recruitment and implementation of the assignment. After eligibility for the study has been confirmed, written informed consent obtained and baseline assessments completed, a 1:1 randomized allocation to either standard stroke care alone (no ventilatory treatment = control) or standard stroke care plus non-invasive ventilatory treatment with auto-BPAP will be performed according to a computer-generated random number (nQuery Advisor® PPS 6.01, Saugus, MA, USA) that is provided via the online Research Electronic Data Capture (REDCap) system [41]. The allocation sequences are concealed from investigators involved in patient recruitment and collection of outcome data. Stratified block randomization with strata for study site and stroke severity as defined by the NIHSS (that is, 4 to 10 and > 10 points) will be used, wherein the block size is fixed and will not be communicated to any of the investigators with clinical involvement in this trial.

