### Secondary endpoints

Tolerability will be assessed by patient adherence to auto-BPAP (defined as tolerating the treatment during sleep or somnolence for at least four hours continuously).

*Safety* will be assessed by:

(i) frequency of serious adverse events (that is, aspiration, aspiration pneumonia defined as combined radiologic, white blood count and clinical findings, respiratory failure with/without intubation) during treatment period that in the opinion of the study physician are causatively and timely (for a maximum of 72 hours from treatment initiation) related to auto-BPAP. For comparison, patients in the control group will be monitored for respiratory complications within 72 hours from randomization. All deaths in both groups during hospital stay;

(ii) frequency of all complaints and possible side effects of auto-BPAP (that is, local irritation of skin/mucosa, mucosal dryness, nausea/vomiting);

(iii) any concerns by hospital nursing staff will be documented as adverse events since patients will be under standard of care repeated assessments set by admission protocols and treating physicians.

Signal-of-efficacy:

Clinical and functional outcomes will be assessed by:

(i) frequency of neurological deterioration (increase in baseline NIHSS score ≥ 4 points) at 24, 48 and after 72 hours from randomization by blinded observers;

(ii) frequency of early neurological improvement (decrease in baseline NIHSS score ≥ 4 points) at 24, 48 and after 72 hours from randomization by blinded observers;

(iii) good functional outcome (mRS score 0 to 2) at discharge and at three months by blinded observers, and ordinal analysis of the mRS at three months;

(iv) all deaths and any TIA or new ischemic stroke during hospitalization or within three months of protocol initiation.

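### Unexpected non-respiratory SAEs have a collection window only once auto-BPAP starts, so controls and active-arm patients who never start have none

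*Protocol article*

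**What the plan says.** All references are to the protocol article.

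- **Collection window (Data Safety Monitoring Board section).** "Serious adverse events (SAE) as described above and unexpected SAE will be collected for the first 72 hours from initiation of auto-BPAP". No other start time is given for unexpected SAEs.
- **Control treatment (Randomization).** Controls are assigned to "standard stroke care alone (no ventilatory treatment = control".
- **Safety endpoint (Secondary endpoints).** In the active arm, the named SAEs (aspiration, aspiration pneumonia, respiratory failure) count when judged "causatively and timely (for a maximum of 72 hours from treatment initiation) related to auto-BPAP". For the other arm: "For comparison, patients in the control group will be monitored for respiratory complications within 72 hours from randomization".
- **Events not limited to one arm (Secondary endpoints).** The safety list includes "All deaths in both groups during hospital stay". The efficacy list includes "all deaths and any TIA or new ischemic stroke during hospitalization or within three months of protocol initiation", and also NIHSS worsening of 4 points or more at 24, 48 and after 72 hours from randomization. Nursing concerns are documented as adverse events, with no arm named.
- **Use of the data (Data Safety Monitoring Board section).** "DSMB will also have access to unblinded data, to make decisions if higher than expected rates of SAEs are being outweighed by potential benefits".

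**The concern.** A window that opens when the device is first used cannot open for a patient who never uses it. Read as written, the rule makes the recording of unexpected SAEs depend on device exposure. It has an opening time for treated active-arm patients, and none for controls or for active-arm patients who never start. The separate control window does not close the gap, because it is confined to respiratory complications. A serious arrhythmia or blood-pressure event in a control would fall under no SAE collection rule.

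Safety is a declared secondary aim, and the trial is meant to inform a phase III study. Patients in the first days of an acute stroke have serious events for many reasons unrelated to ventilation. Without the same ascertainment in controls, an unexpected SAE seen on auto-BPAP cannot be set against what the disease alone produces. The DSMB is asked to weigh SAE rates against benefit, and for this class of event it would do so without a concurrent comparator.

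**Working it through.** The plan gives no figure to reproduce on this point. The main check is to set the rules side by side.

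| Event class | Active, device started | Active, device never started | Control |
|---|---|---|---|
| Named respiratory SAEs | 72 h from device start, if judged related | No start point | 72 h from randomization (respiratory complications) |
| Deaths, TIA, new ischemic stroke | Recorded | Recorded | Recorded |
| NIHSS worsening of 4 points or more | Recorded | Recorded | Recorded |
| Nursing concerns, as adverse events | No arm stated | No arm stated | No arm stated |
| Unexpected non-respiratory SAEs | 72 h from device start | **No window** | **No window** |

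Only the last row is empty for controls.

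**Inputs for an illustration**
- 30 patients per group, 60 in total (Sample size).
- Never-starters: not given. As an assumption, 0 to 20% of the active arm. The 20% is borrowed from the allowance for missing data and tolerability under Sample size, which is not itself a never-start rate.
- Background rate of unexpected non-respiratory SAEs over 72 h: not given. It is assumed equal in both arms, with 5% as the working value. The article expects SAEs overall in fewer than one in ten enrolled patients, so 10% for this class alone would already reach that ceiling.

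**Patients without a window**
- Controls only: 30/60 = 50%.
- With 0.20 × 30 = 6 never-starters: (30 + 6)/60 = 60%.

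**Expected recorded events** = patients with a window × rate
- Active, all start: 30 × 0.05 = 1.5. Chance of at least one: 1 − 0.95^30 = 0.785.
- Active, 24 start: 24 × 0.05 = 1.2. Chance of at least one: 1 − 0.95^24 = 0.708.
- Controls: 30 × 0.05 = 1.5 would occur, and 0 would be collected by rule.
- Lower assumed rate of 2%: 30 × 0.02 = 0.6, with chance of at least one 1 − 0.98^30 = 0.455.

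The counts for starters treat the device as started at randomization. A delay lowers coverage a little. An assumed 6 h delay leaves (72 − 6)/72 = 92% of the first 72 h after randomization. Study procedures requires auto-BPAP within 24 hours of symptom onset, so a 24 h delay would need randomization at the moment of onset and is not a realistic case.

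**The case against.** The strongest reply is that the sentence is loosely worded and that collection in both arms was intended. The same section gives its expected SAE rate per enrolled patient, specifies what follows an SAE for subjects in the auto-BPAP arm (as though SAEs could also arise in the other), requires all SAEs to be reported, and provides monthly safety reports. This is fair as evidence of intent. It still supplies no start time or duration for controls, and it leaves the section inconsistent with itself. Nor is this a detail left to a fuller document: the article states the window and its starting point, and that starting point cannot exist for half of the randomized patients.

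Other parts of the reply stand and set the limits of the point. A reader might infer four stronger conclusions that the article does not support:

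- *Controls have no safety data.* They have respiratory monitoring from randomization, and deaths, TIA, new ischemic stroke and neurological deterioration are recorded in both arms. An intracranial bleed that worsened the NIHSS by 4 points or more would appear as deterioration, though not as a reported SAE. Nursing concerns offer a further, informal route, without an SAE definition or window.
- *A planned comparison of all SAEs will show a false excess on auto-BPAP.* No such between-arm comparison is planned. The stated comparison is of respiratory complications and deaths. The events recorded on auto-BPAP would also be real; what is missing is their counterpart in controls.
- *The halting rule is compromised.* The threshold of more than two per ten patients concerns SAEs resulting from auto-BPAP and needs no control rate.
- *The imbalance is large.* Rates of 10% or 15% for this one class do not fit the article's own expectation for all SAEs together.

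**Conclusion.** The point stands in limited form. For unexpected non-respiratory SAEs, the only stated window opens at device start, so 30 of 60 patients have none (up to 36 of 60 if 20% of the active arm never start). The DSMB's weighing of SAEs against benefit, and the rates passed to phase III planning, would lack a concurrent control rate for this class. At an assumed equal 5% rate, the plan would record about 1.2 to 1.5 events in the active arm and, by rule, none in controls. The gap in the rule follows from the text alone. The event counts rest on the assumed rate and never-start share, neither of which the article gives. It does not make the trial's safety conclusions as a whole uninterpretable, because the main respiratory and vascular events and deaths are covered in both arms. It is worth correcting because ascertainment that depends on exposure cannot be repaired at analysis.

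**What to change.** Reconcile the Data Safety Monitoring Board section with the safety part of Secondary endpoints:

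- Start SAE collection at randomization for every randomized patient, with the same duration in both arms.
- Apply the same event classes in both arms, with unexpected SAEs named explicitly for controls.
- State that active-arm patients who never start the device are included. This also closes the respiratory gap for them, since that endpoint too is timed from treatment initiation.
- Tabulate SAEs by allocated arm in the monthly DSMB reports, which matches the intention-to-treat principle under Planned statistical analysis.

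The change is to wording and to the SAE form, and no treatment rule is touched. The cost is SAE reporting for about 30 control patients in their first days after randomization, when they are inpatients under repeated assessment anyway. Recruitment was already under way when the article was submitted, so events in controls already enrolled would have to be sought in their hospital records.

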### Study procedures

Study physicians will obtain baseline NIHSS scores, determine patient eligibility and obtain informed written consent from each patient prior to any study-related procedures. Patients allocated to the active group will receive non-invasive ventilatory treatment with auto-BPAP (Philips Respironics, Auto-BIPAP Biflex®, Herrsching, Germany) within 24 hours of symptom onset, and for a maximum of 48 hours during diurnal and nocturnal sleep or somnolence, from the beginning of study randomization (Figure 1). This approach warrants that all patients in the active group will receive an intention-to-treat all potential apneic episodes independently of their sleep cycle and somnolence. During the study period, oral and tube feeding intake will be allowed according to local institutional protocols. The auto-BPAP device automatically adjusts expiratory (EPAP) and inspiratory positive airway pressure (IPAP) levels to meet patients’ needs and will be configured to pressure settings that are identical in all patients in the active group: possible minimum EPAP 4 mbar; possible maximum IPAP 25 mbar; maximum difference between EPAP and IPAP (delta) 8 mbar; Biflex 2. The device records sleep-related respiratory events as well as duration of its use. Attachment of the device and initiation of treatment is performed by the study personnel who will receive training specific to the device by a sleep neurologist experienced with the study device.

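### SAE collection and 24-hour DSMB reporting stop 72 h after auto-BPAP starts, leaving later in-hospital deaths and late aspiration pneumonia without that route, and the SAE endpoint carries two conflicting time limits in the active arm

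*Protocol article*

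**What the plan says.** Four time limits in the Protocol article bear on safety.

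- **Treatment** (Study procedures): auto-BPAP is given "for a maximum of 48 hours during diurnal and nocturnal sleep or somnolence, from the beginning of study randomization".
- **SAE endpoint, active arm** (Secondary endpoints, safety item (i)): events count if they occur "during treatment period that in the opinion of the study physician are causatively and timely (for a maximum of 72 hours from treatment initiation) related", with the device as the presumed cause. The listed events are aspiration, aspiration pneumonia and respiratory failure. Aspiration pneumonia requires imaging, white-cell and clinical findings together.
- **SAE endpoint, controls, and deaths** (same item): controls are watched for respiratory complications for 72 h from randomization. The item closes with "All deaths in both groups during hospital stay".
- **SAE collection** (Data Safety Monitoring Board): listed and unexpected SAEs "will be collected for the first 72 hours from initiation of auto-BPAP". Each one must reach the DSMB within a day of happening, and incident details are submitted for adjudication. An SAE in the auto-BPAP arm also ends treatment for that patient.

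The DSMB has other sources: "Thereafter, DSMB will receive monthly enrollment/safety/outcomes reports", it can be convened whenever a concern arises, and it can see unblinded data.

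**The concern.** Aspiration pneumonia is a named risk of the intervention. Its definition needs three kinds of finding, so it may be met some time after exposure. A collection window counted from the start of treatment can close before that happens. Death is followed over a longer horizon than the complications that might explain it, so a late death can appear in the safety results with no adjudicated event beside it.

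The second issue is comparability. If the treatment-period wording is applied as written, the active arm is observed for less time than the control arm on the respiratory events that matter most. That error would make auto-BPAP look safer than it is. Safety is a stated secondary aim and the trial is meant to inform a phase III study, so the counts should cover equal windows in both arms.

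**Working it through.** **Inputs.** Treatment cap: 48 h from randomization (Study procedures). SAE window: 72 h from initiation (DSMB section and safety item (i)). Control window: 72 h from randomization (safety item (i)). Arm size: 30 (Sample size). The delay *d* from randomization to the start of auto-BPAP is not given. Treatment must start within 24 h of symptom onset, so *d* is assumed to lie between 0 and 24 h.

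**Step 1: does the SAE window cover treatment?** Counted from initiation, treatment ends no later than 48 − *d*. Collection then continues for 72 − (48 − *d*) hours.

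| *d* (h, assumed) | Latest end of treatment, h from initiation | Collection remaining after that (h) |
|---|---|---|
| 0 | 48 | 24 |
| 6 | 42 | 30 |
| 12 | 36 | 36 |
| 24 | 24 | 48 |

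The window always covers all permitted treatment and at least 24 h more. If the 48 h cap is read as running from initiation, the remainder is 72 − 48 = 24 h for any *d*.

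**Step 2: the two limits in safety item (i).** Under the treatment-period limit the active arm is counted for at most 48 − *d* hours, against 72 h for controls. The shortfall is 72 − (48 − *d*): 24 h at *d* = 0 (24/72 = one third of the window) and 48 h at *d* = 24 (48/72 = two thirds). It is larger still if treatment ends early. Under the 72 h limit the shortfall is 0. One sentence supports both readings.

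**Step 3: what happens after hour 72?**

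| Event first present after hour 72 | Recorded? | 24-hour report and adjudication? |
|---|---|---|
| In-hospital death | Yes: safety item (i), and signal-of-efficacy item (iv) to three months | None stated |
| Aspiration pneumonia, no earlier recognised aspiration | No stated capture as an SAE | None stated |
| Aspiration pneumonia after an aspiration recognised within 72 h | The aspiration is itself a listed SAE, subject to the physician's attribution | Yes, for the aspiration |

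**Step 4: weight of one event.** 1/30 = 3.3 percentage points in an arm.

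**The case against.** The best defence is that the plan is less exposed than it looks, and much of that defence stands.

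- A reader might infer that DSMB oversight closes at 72 h. It does not. The monthly safety and outcome reports, the provision that the "DSMB will be convened any time that safety or data concerns arise", and the statement that the "DSMB will also have access to unblinded data" carry no 72 h limit. The text does not say, however, that the monthly reports list late deaths, and none of these routes requires adjudication.
- A reader might infer that late deaths are lost. They are recorded in both arms under two endpoints. What they lack is a prompt route, not ascertainment.
- A reader might infer that the 48 h treatment cap conflicts with the 72 h collection window. Step 1 shows that it does not.
- A reader might take a patient who aspirates at hour 47 and dies of pneumonia on day 5 as an event the DSMB never hears of. Aspiration is listed separately from pneumonia, so if it is recognised and attributed to the device it enters the SAE process in time. The gap is confined to pneumonia without an earlier recognised aspiration.
- It can be said that the 72 h parenthesis in safety item (i), repeated in the DSMB section, settles the loose reference to the treatment period. That is probably what was intended. But the sentence states both limits, and only one of them gives the arms equal length.
- A longer horizon for deaths than for device-related SAEs is not in itself a contradiction. That is right; the point is the missing route, not the difference.

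**Conclusion.** The point holds in a limited form. SAE collection, and with it expedited reporting and adjudication, ends 72 h after initiation. Beyond that hour, in-hospital deaths have no 24-hour route, and aspiration pneumonia first meeting its definition has no stated capture as an SAE. Separately, the double limit in safety item (i), applied literally, shortens active-arm counting by at least 24 of 72 h and biases the comparison in favour of auto-BPAP. If the 72 h limit is taken to govern, that bias disappears.

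The number of affected events cannot be derived from the document. The window figures rest on the assumed range for *d*. Mortality counts are not impaired, and no result is shown to change. This should be corrected because the correction is cheap and the safety counts are small.

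**What to change.** 1. In Secondary endpoints, safety item (i), delete the words that restrict events to the treatment period, so that a 72 h comparison window applies in both arms.
2. Keep that window as the main comparison. In addition, record aspiration, aspiration pneumonia, respiratory failure and other SAEs in both arms to hospital discharge, the horizon already used for deaths, and report them as a supplementary count.
3. In the DSMB section, make every in-hospital death, on any day and in either arm, reportable to the DSMB within 24 hours.
4. Leave the SAE halting rule and its tally as they are. All-cause deaths should not be added to it: the rule concerns SAEs resulting from auto-BPAP, with an expected rate drawn from the pilot, and adding background stroke deaths would change what it counts.

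The cost is a wording change in two sections and a record check at discharge, when the mRS is already assessed. The supplementary count will pick up more background stroke complications, which is why the 72 h window remains the main comparison.

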### Sample size

Sample size estimates were calculated from a previous randomized feasibility study [37], where a significantly greater improvement in the NIHSS score was observed when AIS patients were treated with CPAP as compared with controls (mean 2.3 versus 1.4 points, *P* = 0.022). This minimal difference of 0.9 points in NIHSS improvement between the groups was considered clinically relevant. Assuming a two-sided 5% significance level and 80% power, 24 patients in each group (48 patients in total) would be needed to detect such a difference in the mean NIHSS score at 72 hours (nQuery Advisor ® 6.01, Saugus, MA, USA). In order to reflect missing data and possible issues with tolerability (for example, loss to follow-up, lack of patient compliance) at a maximum rate of 20%, the sample size for this study is set at 60 patients (30 per group).

To minimize missing data in this trial, all outcome assessments will be electronically scheduled for each enrolled patient and reminders will be electronically generated and delivered to the assessors on time. Also, to prevent drop-outs due to non-compliance with auto-BPAP in the active treatment arm, patients will be closely monitored by a carefully trained nurse to enhance tolerability of the auto-BPAP device. After discharge, all patients will be contacted and interviewed either face-to-face or by telephone. In patients who are not able to communicate, proxies will be involved.

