Maintenance of stable systemic and cerebral hemodynamics, as well as adequate and constant brain tissue oxygenation, plays a crucial role in the management of AIS [32]. The ischemic penumbra may be present for many hours and be amenable to reperfusion. Consequently, any treatment that potentially maintains or augments cerebral perfusion may be justified [33]. Non-invasive ventilation with either continuous (CPAP) or bilevel positive airway pressure (BPAP) is the treatment of choice for sleep apnea. Although some studies have shown the safety and beneficial effects of CPAP and BPAP by improvement of quality of life and reduction of cardio- and cerebrovascular morbidity and mortality in the general sleep apnea population [34,35], their role in AIS patients remains to be elucidated. Most previous investigations were conducted beyond the (hyper-) acute phase of ischemic stroke and pursued secondary stroke prevention goals rather than acute effects. For example, two studies confirmed safety and tolerability, and pointed to a potential short-term treatment effect of prompt initiation of non-invasive ventilation in the acute phase of stroke when hemodynamically compromised tissue can potentially be salvaged [36,37]. In the first study, an observational study, AIS patients with proximal persisting arterial occlusions and suspected or known OSA had a tendency towards early neurological improvement (median National Institutes of Health Stroke Scale (NIHSS) score decrease by 2 points) during the hospital course when BPAP was initiated within the first 24 hours of admission, as compared with those who did not receive BPAP (median NIHSS score decrease by 1 point, *P* = 0.078) [36]. The other study randomly assigned fifty patients in the first night after AIS to either CPAP for three nights or control [37]. The investigators found that CPAP treatment was feasible, safe and associated with a greater neurological improvement until day eight in patients who tolerated CPAP well when compared with control patients (NIHSS 2.3 versus 1.4, *P* = 0.022).

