### Planned statistical analysis

Research Electronic Data Capture (REDCap) [41] will be used for recruitment and data management in this study. The primary analysis will be an intention-to-treat analysis in which all subjects are retained in the group to which they were allocated and included in the analysis, irrespective of their compliance with allocated treatment. Statistical analysis in this population is used to determine statistical significance. The per-protocol population with inclusion of all patients without major protocol violations will be also analyzed. For confirmatory analysis, the primary endpoint will be assessed using the Mann-Whitney *U-*test. For secondary endpoints, categorical variables will be assessed using Chi-square tests or Fisher’s exact test, while continuous variables will be assessed using Student’s *t*-test and the Wilcoxon rank sum test, where appropriate. With regard to the exploratory analysis, adjustments will not be made for multiple comparisons. Multivariate analysis will be performed to define positive and negative predictors of specific primary and secondary outcomes. Last-observation-carried-forward method will be used to impute missing data. Statistical significance will be declared if the two-tailed *P*-value will be less than 0.05. Two-sided 95% confidence intervals will be calculated for continuous variables. All statistical analyses will be performed with SPSS (SPSS Inc., Chicago, IL, USA) and SAS (SAS Institute, Inc., Cary, NC, USA) software.

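### The 0.9-point planning effect is reported elsewhere in the article for patients who tolerated CPAP, and the 20% allowance treats non-compliers as lost although ITT keeps them, so the single 80% power figure should be a range conditional on compliance

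*Protocol article*

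**What the plan says.** All references are to the protocol article.

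- **Background.** The earlier randomized feasibility study is reported as showing more improvement "until day eight in patients who tolerated CPAP well when compared with control patients (NIHSS 2.3 versus 1.4". The contrast is between patients who tolerated the treatment and controls, followed to day eight.
- **Sample size.** The same two means and the same P-value reappear, but now "a significantly greater improvement in the NIHSS score was observed when AIS patients were treated with CPAP as compared with controls". Neither tolerance nor day eight is mentioned, and the difference is applied to the mean NIHSS score at 72 hours. The section adds: "This minimal difference of 0.9 points in NIHSS improvement between the groups was considered clinically relevant".
- **Sample size, power.** "Assuming a two-sided 5% significance level and 80% power" gives 24 per group. No SD is stated.
- **Sample size, inflation.** Missing data and non-compliance share one allowance: "lack of patient compliance) at a maximum rate of 20%, the sample size for this study is set at 60 patients".
- **Planned statistical analysis.** The primary analysis is intention-to-treat and includes all patients "irrespective of their compliance with allocated treatment". The test is Mann-Whitney, and missing values are filled by last observation carried forward.

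**The concern.** Three statements do not fit together. The planning effect comes from a group selected for tolerating treatment. The allowance for poor tolerance is computed as if those patients disappear. The analysis that decides significance keeps them.

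A patient who leaves the analysis costs sample size, and dividing by one minus the loss rate repairs that. A patient who stays in the active arm untreated costs effect size. If a fraction f gets no benefit, the difference shrinks by (1 − f) and the required sample grows by about 1/(1 − f)². The plan makes the first correction where, for non-compliance, the second is needed.

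What is at stake is how the result is read. A non-significant finding would be judged against a stated 80% power that the trial may not have for the comparison it actually makes.

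**Working it through.** **Inputs from the article:** two-sided 5% level; 80% power; difference 0.9 (2.3 − 1.4); 24 per group before and 30 per group after inflation; 1:1 allocation; ITT; Mann-Whitney test.

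**Assumptions, not in the article:** the SD, and the share of the 20% that is non-compliance.

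**1. Reproduce the plan.** 48/0.8 = 60, so the inflation step is reproduced exactly. The 24 per group cannot be checked independently without an SD. Solving backwards for 80% power at 24 per group gives a standardized difference of 0.826 with the t-test, so SD = 0.9/0.826 = 1.09. The normal approximation gives 0.9 × √(24/2)/(1.960 + 0.842) = 1.11.

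**2. Dilute the effect.** If a fraction f of the active arm stays in the analysis with the control-arm mean, the ITT difference is 0.9 × (1 − f):

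- f = 0.10: 0.81 points, standardized 0.744
- f = 0.20: 0.72 points, standardized 0.661

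**3. Power with 30 per group analysed, SD 1.09.** The second column uses an effective sample of 30 × 0.955. The simulations draw normal scores, with the non-compliers in the active arm at mean 1.4.

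| Non-compliant, no benefit | t-test | Mann-Whitney, asymptotic efficiency | Mann-Whitney, simulated | Simulated, scores rounded to integers |
|---|---|---|---|---|
| 0% | 88% | 87% | 86% | 84% |
| 10% | 81% | 79% | 78% | 75–76% |
| 20% | 71% | 69% | 67% | 64–65% |

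With SD 1.11 the 20% row falls by about two points (t-test 69%; rounded simulation 62%).

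**4. Sample needed at f = 0.20.** For 80% power, 36.9 per group (t-test), or 36.9/0.955 = 38.7 (Mann-Whitney). The rule of thumb agrees: 24/0.8² = 37.5. The plan has 30.

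**5. Other ways to fill the joint 20%.**

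- 10% missing and excluded plus 10% non-compliant: about 70–76%.
- All 20% missing and excluded: 24 per group remain, about 76–80%.
- All 20% missing and carried forward as no change from baseline: about 56–63%.
- All 20% missing and carried forward at half the final improvement: about 79–83%.
- 20% non-compliant with half the benefit: the difference is 0.9 × (1 − 0.20 × 0.5) = 0.81, giving 81% (t-test) or 79% (Mann-Whitney, asymptotic efficiency).

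**The case against.** **The inflation already gives some cover.** This stands. With 60 patients and full compliance, power is above 80%, and at 10% zero-benefit non-compliance it is still close to 80%. A reader might infer that 80% holds only if every patient complies; the figures above refute that.

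**The 64–71% is one corner.** This also stands. The 20% is a maximum and covers missing data as well as compliance. The Secondary endpoints section defines adherence as at least four continuous hours, so a non-adherent patient may still have been treated and may benefit in part. A reader might call 64–71% the trial's true power. The article does not support that, because it gives neither the SD nor the split of the 20%.

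**The source study may have shown an effect in everyone randomized.** A reader might infer that the effect was seen only in tolerators. The Background reports the tolerators' result and is silent on the rest, so that cannot be said.

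**Phase III is not affected directly.** A reader might infer that a later trial would inherit the tolerance-selected 0.9. The Discussion says phase III is to be powered from this trial's own data, and the primary analysis here is ITT.

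**0.9 points can be read as a target of clinical relevance.** On that reading, the power for a true ITT difference of 0.9 is not wrong. But the section also derives the figure from the earlier study and describes that result differently from the Background, and the handling of non-compliance remains at odds with ITT on either reading.

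**Conclusion.** The point holds as a mismatch of assumptions, not as an arithmetic slip: 48/0.8 is indeed 60. The Sample size section drops two qualifiers that the Background attaches to the same result (tolerance, and day eight), and it corrects for non-compliance in a way that the ITT analysis does not allow.

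In size, 30 per group gives about 84–88% power with full compliance and data, about 75–81% at 10% non-compliance without benefit, and about 64–71% if the whole 20% maximum is such non-compliance. The top of each range is the t-test; the rest is the planned Mann-Whitney test under different approximations. The ranges rest on an SD of about 1.09 recovered from the plan's own 24 per group, on complete data, and on zero benefit in non-compliers. Partial benefit raises the last two; missing data can move them either way. The effect of moving from day eight to 72 hours cannot be quantified from the article and is not included.

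**What to change.** In the Sample size section:

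1. Describe the source effect as the Background does: patients who tolerated CPAP against controls, until day eight. Say that applying it at 72 hours is an assumption.
2. State the SD used to obtain 24 per group.
3. Give separate rates for missing data and for non-compliance. Divide by one minus the rate only for patients who truly leave the analysis.
4. Replace the single 80% with the conditional power of the ITT Mann-Whitney comparison at 30 per group. With an SD of 1.09 that is about 84–87% with full compliance and data, 75–79% with 10% of the active arm non-compliant without benefit, and 64–69% with 20%, higher if non-compliers benefit in part. Recompute if the SD actually used differs.

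Keep 60 patients. No endpoint, analysis or design feature changes. The cost is one rewritten paragraph and a less favourable stated power.
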